## Discussion

### Adherence strategy

The compliance strategy starts with determining how to improve the adherence of participants and the intervention implementers (community managers).

Before the implementation of the project, the study group conducted a series of compliance tests using a series of combination methods to include participants with high compliance in the study. Community managers must not only have a certain level of medical professionalism, but they must also be emotionally intelligent, agreeable, and able to maintain a good and harmonious relationship with participants. During the study, core information on health behaviors will be published daily in the online WeChat group to increase crowd adherence. The research team will prepare appropriate holiday gifts for the participants (inexpensive but meaningful, such as a flower for all subjects on Mother’s Day, etc.). If participants raise questions in the online WeChat group, the community manager should respond in time (generally within 10 min) and provide positive feedback. After the group intervention, the community manager instructed the participants to communicate with one another to increase the bonding effect of the intervention at the level of peer effect. For participants who completed 100%, 90%, and 80% of the intervention content, various reward strategies, such as “fast track” appointments and “face-to-face” expert consultations, will be provided. The community manager will be responsible for counting the participation times of the participants and publishing the times and ranking situation in the WeChat group online every week (usually on Friday).

Although the outcome of the study is very important, the characteristics of the staff in the implementation process, such as the identification of the values of the study, the degree of implementation of the research protocol, and other factors, are important influencing factors that determine the success of the study. Each group requires a consistent community manager who cannot be changed frequently.

All subjects are not allowed to participate in other lifestyle intervention or drug intervention trials during this study period. During the study period, if a subject does participate in another lifestyle intervention or drug trial, we will inform them that although they can continue to participate in the program, they will not be provided with follow-up evaluations and related tests (fMRI, blood tests, etc.) and their personal data will be disregarded and not used in the analysis.

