### Explanation for choice of comparators

The main aim of this study is to evaluate the effectiveness of multidomain cognitive intervention. Subjects in the non-contact control group (without any intervention) will be selected as the control group to compare the effect evaluation of different intervention intensification (multi-domain collaborative intervention and traditional health education).

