#### Randomization, allocation and concealment

The roles involved in the implementation of the study in each sub-center included PI, data platform manager, participant, community manager (research team), community partner, multidimensional intervention implementation team, health education implementation team, cognitive assessment team, and radiology testing team. A computer generator randomizer method (PI execution) is used to determine the intervention content in each community, and PI is responsible for conducting specific research work in each sub-center. This study could not achieve a perfect “blinding” because the participants are able to clearly perceive the intervention, but we tried to maximize the “isolation” of the intervention/control implementation team in each group to reduce the interaction between the groups.

The intervention/control settings of the three communities in each sub-center are assigned by the platform manager using the computer generator randomizer method to achieve the randomization process in our study.

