#### Statistical methods

To compare the results of cognitive assessment among groups, quantitative data analysis will use IBM SPSS version 21.0 [27] and Python version 3.0 [28] software, relying on the analysis of variance, covariance, and other methods. Mean, standard deviation (SD), median, and range will describe continuous variables. Counting, proportion, the Wilcoxon test, and other methods will be used to analyze categorical variables. Classify and compare the normal distribution, homogeneity of variance and other data features of each variable in all the data, preliminarily screen variables with statistical differences, and combine professional knowledge to use these variables as alternative variables for subsequent comparative analysis and model training. Graphical summaries such as boxplots, case profiles, and labeled dispersion maps will be used to compare the distribution of intervention variables in each group and participant characteristics between groups. A linear mixed model will be used to simulate longitudinal changes in primary responses between groups, allowing for missing data (assuming data is missing at random) and within-subject correlations for repeated measures over time, with the model adjusting for baseline response variables and other covariates as needed. The effectiveness analysis (Full Analysis Set, Per Protocol Set) will be performed to assess the overall effect of the intervention.

Using data analysis techniques such as regression, chi-square, T-test, rank-sum test, normality test, decision tree, support vector machines, XGBoost, CATBoost and artificial intelligence deep learning, this study will rely on multi-modal data, take training effect and cognitive improvement as label values, and build a prediction and intervention model of mild cognitive dysfunction supported by artificial intelligence technology. Simultaneously, our team will apply explicable machine learning theory to explain the variables in the model and try to create new ideas for the basic research direction.

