#### Data acquisition

The questionnaire assessment and equipment testing are important quality control links in the assessment section.

Only evaluators who pass the assessment can enter the community to assess the older-adult residents. The data platform manager completes the setup of online evaluation tools, including content construction, cell restriction, logic jump setting, and review, before entering the community to conduct the evaluation. The questionnaire assessment process of each community resident will be completed independently by a fixed questionnaire assessor (trained student volunteers), and the evaluation method will be a community on-site assessment. And resident must answer all questions, and no family members or other people are permitted to do so. The current students will be hired as the “third independent person” telephone return visitors the day after the on-site assessment, and 20% of the evaluated participants on the day are randomly selected to conduct a second telephone inquiry and check on some core questions in the questionnaire (the daily check content is randomly generated, and the telephone return visit time is approximately 1–3 min).

Equipment quality control uses unified brand instruments and equipment to measure suitable indicators. Standard operating procedures for instruments and equipment can help different operators follow the same procedures. Before using the instrument, it should be debugged and corrected, and records should be kept for future reference. In principle, it is recommended that all instruments be operated by fixed operators or that uniform training and assessment be provided. For data traceability, all data generated by instruments and equipment must be accurately recorded and backed up. The data copy principle is “today’s data, and today’s copy”, which is stored in a special mobile hard disk owned by PI and backed up to the data platform manager.

In the face of missing data due to uncontrollable factors, the following steps should be taken to trace, retest or deal with it to minimize the loss: [1] Discuss the reasons for missing data and potential remedies within the project team; [2] Attempts to find historical data or contact subjects for data tracing or retesting; [3] If it is really impossible to make up for the missing data, the project team members shall discuss and determine whether to eliminate the data or use statistical methods to make up for it.

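### Participants who join another trial are refused the exit evaluation and dropped from the whole analysis, not only from the Per Protocol Set

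*Protocol article*

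**What the plan says.** The Adherence strategy section forbids taking part in other lifestyle or drug intervention trials, and then provides for breaches. The trigger is a post-enrolment event: "During the study period, if a subject does participate in another lifestyle intervention or drug trial". The participant may carry on with the programme, but "they will not be provided with follow-up evaluations and related tests (fMRI, blood tests, etc"). In addition, "their personal data will be disregarded and not used in the analysis". No analysis set is named.

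Three other places bear on this rule:

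- **Data collection methods** plans the cognitive, physical, imaging and biological assessments for every formally enrolled participant, once on entry and once on exit.
- **Statistical methods** states: "The effectiveness analysis (Full Analysis Set, Per Protocol Set) will be performed to assess the overall effect of the intervention". Neither set is defined in the article. The same section plans a linear mixed model, "allowing for missing data (assuming data is missing at random").
- **Data acquisition** says that, when a missing value can be neither traced nor retested, "the project team members shall discuss and determine whether to eliminate the data or use statistical methods to make up for it".

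**The concern.** A Full Analysis Set is ordinarily meant to keep allocated participants in the arm to which they were allocated, whatever they do later. A breach such as joining another trial is usually a reason to leave the Per Protocol Set only. Here the breach removes the person from the analysis altogether, and the outcome is never measured.

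The trigger could be related to arm. On masking, the article says: "This study could not achieve a perfect “blinding” because the participants are able to clearly perceive the intervention". On the comparator, it says: "Subjects in the non-contact control group (without any intervention) will be selected as the control group". The multidomain arm, by contrast, has exercise and meditation sessions three times a week. How often people look for or accept another trial could therefore differ between arms, and so could the kind of person who does. If either differs, the participants left in each arm are no longer comparable in the way that allocation made them.

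The loss is also permanent. An exit assessment not done at six months cannot be recovered, and the article dates the formal multicentre phase from February 2023 to December 2024.

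**Working it through.** The article gives no figure on this point to reproduce. The check has two parts: the sections set side by side, and an illustration of size under stated assumptions.

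**1. The sections side by side**

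| Question | Adherence strategy | Elsewhere in the article |
|---|---|---|
| Is the exit assessment done? | No, for those who join another trial | Yes, for all formally enrolled (Data collection methods) |
| Are their data analysed? | No, in any set | Full Analysis Set and Per Protocol Set both planned (Statistical methods) |
| How is a missing exit score handled? | The person's data are dropped | Mixed model under missing at random (Statistical methods) |

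The first row is a direct conflict. The second is a conflict with the usual meaning of the Full Analysis Set, because the article does not define it. On the third, the mixed model cannot rescue these people. As far as the text shows (the timeline figure is not available), outcomes are measured only at enrolment and exit. Without the exit visit there is no post-baseline outcome, and the rule discards the baseline as well.

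**2. Illustration of size**

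Let q be the proportion deleted in an arm, and D the mean exit score of those deleted minus the mean of those retained, in SD units. The full-arm mean equals the retained mean plus qD. For the contrast multidomain minus control:

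shift caused by deletion = q_control × D_control − q_multidomain × D_multidomain.

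With the same D in both arms this is (q_control − q_multidomain) × D. All values of q and D below are assumptions. The arm size is from the article: 12 sub-centers × 30 = 360.

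| Assumed q, control v multidomain | People deleted, of 360 each | Assumed D (SD) | Shift (SD) |
|---|---|---|---|
| 10% v 2% | 36 v about 7 | 0.5 to 1.0 | 0.08 × 0.5 = 0.04 to 0.08 × 1.0 = 0.08 |
| 3% v 1% | about 11 v about 4 | 0.25 to 0.5 | 0.02 × 0.25 = 0.005 to 0.02 × 0.5 = 0.01 |
| 5% v 5% | 18 v 18 | any, same in both arms | 0 |

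Reversing the sign of D, or the order of the rates, reverses the sign of the shift.

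**3. What such a shift does to a test**

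Take no true effect, a two-sided 5% z-test, and 360 × 0.8 = 288 per arm after the planned 20% dropout, which is 288/12 = 24 per community. Assume an intracluster correlation of 0.01 (the article gives none) and no gain from baseline adjustment. Then SE = √[(2/288) × (1 + 23 × 0.01)] = 0.092 SD. The rejection rate is Φ(−1.96 + shift/SE) + Φ(−1.96 − shift/SE):

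- shift 0.01: 5.1%
- shift 0.04: about 7%
- shift 0.08: about 14%

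So the effect on the error rate runs from negligible to material, depending wholly on the assumed inputs.

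**The case against.** The strongest reply is that few people will be affected. The rule reaches only those who breach an explicit ban. The exclusion criteria already remove people who plan to join, or have joined, concurrent drug or exercise trials. Recruitment selects for compliance in several steps, participation lasts six months, and communities are more than 5 km apart and unaware of one another, so controls have less reason to feel passed over. The model also adjusts for baseline, which would absorb part of any selection difference. All of this stands. It lowers the likely size of the bias but does not remove the conflict, because the article itself provides for later joiners.

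A second reply is that the Full Analysis Set may be defined elsewhere. That is fair, and the missing definition is not part of this point. A reader might infer that no Full Analysis Set can be built at all. The article does not support that: what it shows is a conflict with the ordinary meaning of the term. Even so, a definition elsewhere could not supply exit scores that this rule prevents from being collected.

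A reader might also infer that the Data acquisition section lets the team delete observed data, or put historical values in place of exit scores. It says neither. It concerns values that stay missing after tracing and retesting, and the mention of historical data reads most naturally as recovering lost records. Nor is it a strict contradiction of the mixed model, since leaving an irrecoverable value out, or filling it in statistically, can both be compatible with missing at random. What remains is that the choice has no stated criterion, while Statistical methods already names an approach.

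**Conclusion.** The point holds for the Adherence strategy rule. As written, it withholds a planned outcome and removes allocated participants from every analysis because of something that happens after allocation. It is at odds with the Data collection methods section and with what a Full Analysis Set ordinarily means.

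The rule can bias the arm comparison, but the documents do not show that it will. Joining rates, the outcomes of joiners and the direction are all unknown. The illustrations run from 0.005 to 0.08 SD, and the shift is zero if rates and outcomes are alike across arms. It is tempting to conclude that the rule favours the intervention because controls are free to seek help elsewhere. The article does not support that: controls are under the same ban, and the sign depends on whether joiners would have done better or worse than the rest.

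The ban on concurrent trials is not at fault. The open choice in the Data acquisition section is a secondary matter of alignment.

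**What to change.** Amend the Adherence strategy section so that a participant who joins another lifestyle or drug trial:

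- is still offered the planned exit evaluation;
- stays in the Full Analysis Set under the arm of their community;
- has the event and its date recorded;
- is excluded only from the Per Protocol Set.

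The ban itself can stay as it is.

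As a secondary change, align the Data acquisition section with Statistical methods: state that exit values which cannot be recovered are handled by the mixed model under missing at random, and not by a case-by-case choice of the team.

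The cost is a few sentences and a small number of exit tests that the Data collection methods section already plans for everyone enrolled. The sample size does not change. The amendment is worth making while exit visits are still to come.

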### Quality control

Quality control methods (online + offline) included regular study progress meetings (WCHSCU & sub-centers Principal Investigator (PI)), methodology training, “regular flight supervision” (The research team will travel from Chengdu to the city where the sub-center is located to supervise the ongoing research, and the supervision frequency is once every 6–8 months to ensure the quality of the research), experience sharing, and exchange discussion (multidimensional intervention group, health education group, and non-contact control group are carried out independently). The core points for quality control of each sub-center are as follows.

#### Participants and communities

The main goal of subject-level quality control is to screen the subjects according to the eligibility criteria, implement the project strictly according to the research plan, take the initiative to understand the feelings, questions, and appeals of the participants during their participation in our program, and establish a good relationship between the community research manager and the participants on the premise of not interfering with the whole research.

The distance between any two research communities should be greater than 5 km to avoid the influence of contamination factors on the research. In the present study, community partners must meet the following criteria: [1] have independent office areas (such as non-governmental organizations or property service centers) in the study community; [2] have an excellent community-friendly foundation and have carried out resident activities in the community; and [3] cooperate with the research team to provide support for publicity and intervention sites within the community.

#### Groups perform standards and quality control

During the intervention phase, community managers and the PI will be jointly responsible for quality control. Community managers will be responsible for communicating with the intervention implementation team, community partners, and participants to confirm the site, time, and staffing arrangements related to the intervention to meet the objective conditions for implementing the study protocol. The following are the key quality control points in each group.

Multidimensional intervention group [1]. All intervention activities should be completed in the community of the participants [2]. The exercise intervention will be taught alternately by two coaches, with no additional coaches added during the intervention. The exercise training will be taught according to the training schedule, and the training plan will not be altered during the course. After each training, the coach will give the participants positive motivation and encouragement and collect the subjects’ training feedback. To guide and correct the training movement standards, the number of participants in each offline training intervention cannot exceed 30; if there are > 30 participants, two coaches must be present simultaneously to ensure that each participant receives enough attention. The weekly intervention time should be fixed and remain unchanged. To achieve adequate training supervision, the training coach will use the sports watch to monitor the heart rate and other indicators of the participants [3]. Meditation intervention requires the preparation of meditation tasks (instructions and background music) in advance, and the same meditation task cannot be repeated within a month. The meditation training began within 5–10 min of the end of the exercise intervention.

The participants will be reminded not to sleep before meditation. After completing the meditation, it is necessary to guide the subjects to communicate with one another about their meditation feelings, which is beneficial to developing a social support network in the intervention group. At the end of all courses, feedback from the participants will be collected. Participants will be encouraged to practice self-training meditation [4]. The quality control of the dietary intervention focused on supervising and encouraging subjects to eat according to the recipes. Community managers will be responsible for encouraging participants to send photos of three meals daily to monitor whether they eat according to the recommended recipes. To avoid the awkward situation of different recipes in one family, the same family members’ recipes are consistent. Community managers will provide one-on-one supervision and encouragement to participants who do not post food photos [5]. To improve the sleep behavior of the participants, the community managers regularly pushed popular science articles on the topic of “sleep health” in the online WeChat group (once a week). There will be a free community on-site consultation with a sleep specialist. Instead of traditional passive knowledge dissemination (such as non-interactive “PPT teaching”), offline health lectures take the form of interactive teaching.

Health education group [1]. All intervention activities should be completed in the community of the participants [2]. The six-month health education course is completed by six doctors, which facilitates PI supervision of teaching quality and the maintenance of subject compliance [3]. The weekly course time is fixed (2 to 3 pm every Wednesday) and cannot be changed [4]. Every Monday, community managers remind the details of course time, place, teaching topic, and teaching teacher information in the online WeChat group [5]. One-on-one communication will be conducted to encourage participants who have failed to come or requested leave for two consecutive times to avoid dropping out [6]. During traditional Chinese festivals, small gifts will be prepared according to the festival atmosphere for participants to improve their compliance and recognition of this study.

Non-contact control group [1]. whether to prepare small gifts for participants during traditional Chinese festivals; [2] The number of subjects in this group should be increased appropriately (by about 10%) to cope with the dropout due to uncontrollable factors.

#### Data acquisition

The questionnaire assessment and equipment testing are important quality control links in the assessment section.

Only evaluators who pass the assessment can enter the community to assess the older-adult residents. The data platform manager completes the setup of online evaluation tools, including content construction, cell restriction, logic jump setting, and review, before entering the community to conduct the evaluation. The questionnaire assessment process of each community resident will be completed independently by a fixed questionnaire assessor (trained student volunteers), and the evaluation method will be a community on-site assessment. And resident must answer all questions, and no family members or other people are permitted to do so. The current students will be hired as the “third independent person” telephone return visitors the day after the on-site assessment, and 20% of the evaluated participants on the day are randomly selected to conduct a second telephone inquiry and check on some core questions in the questionnaire (the daily check content is randomly generated, and the telephone return visit time is approximately 1–3 min).

Equipment quality control uses unified brand instruments and equipment to measure suitable indicators. Standard operating procedures for instruments and equipment can help different operators follow the same procedures. Before using the instrument, it should be debugged and corrected, and records should be kept for future reference. In principle, it is recommended that all instruments be operated by fixed operators or that uniform training and assessment be provided. For data traceability, all data generated by instruments and equipment must be accurately recorded and backed up. The data copy principle is “today’s data, and today’s copy”, which is stored in a special mobile hard disk owned by PI and backed up to the data platform manager.

In the face of missing data due to uncontrollable factors, the following steps should be taken to trace, retest or deal with it to minimize the loss: [1] Discuss the reasons for missing data and potential remedies within the project team; [2] Attempts to find historical data or contact subjects for data tracing or retesting; [3] If it is really impossible to make up for the missing data, the project team members shall discuss and determine whether to eliminate the data or use statistical methods to make up for it.

